### **3.6 Statistical Analysis**

Descriptive statistics will include the Chi-squared test or Fisher exact test for categorical variables expressed as frequency. Assessment for normal distribution will be performed with the Shapiro–Wilk test. Normally distributed data will be presented as mean and standard deviation (SD) and compared by the independent sample t-test. Non-normally distributed data will be presented as median and interquartile range (IQR) and compared by the Mann-Whitney U test.

For data collected at multiple time points, we will adopt the Generalized Estimating Equations (GEE). First, we will test the interaction between treatment and time. If this interaction is significant, we will test the between-group differences at each time point and use the Bonferroni test to adjust for multiple comparisons. Otherwise, we will next test the main effect of treatment, and the Bonferroni correction will not be performed for the treatment effects at each time point. For the comparison of the incidence rate of moderate to severe postpartum contraction pain, the GEE model will include the following settings: covariates: intervention group, time, intervention  $\times$  time interaction; link function: logit function; group variable: participant; intraclass

correlation structure: independent. The GEE models for contraction pain score, incision pain score, depression score, anxiety score, sleep score, and recovery quality score will include the following settings: covariates: intervention group, time, intervention  $\times$  time interaction; link function: identity link; group variable: participant; intraclass correlation structure: independent. Data will be analyzed using SPSS version 27.0 (IBM Corp., Chicago, ILUSA) and GraphPad Prism V.9 (GraphPad Software, San Diego, CAUSA), with  $P < .05$  considered statistically significant.

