### **3.5 Outcome measures**

#### **3.5.1 Primary outcome**

The primary outcome is the incidence of moderate to severe uterine contraction pain on the third postoperative day. Pain intensity is evaluated using the Visual Analogue Scale (VAS). The VAS is a well-established tool for evaluating pain, consisting of a 100 mm line where one end represents "no pain" and the other end signifies "the worst pain imaginable" or "the most extreme pain possible". Participants are asked to mark the point on the line that best corresponded to their perceived pain intensity. In this study, uterine contraction pain is classified as moderate to severe if the VAS score is 4 or higher.

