### **3.7 Sample Size Calculation**

Based on our preliminary observation, the incidence of moderate to severe uterine contraction pain on the third postoperative day following a lower-segment transverse cesarean delivery is approximately 35% (7 out of 20 patients). Considering that the number needed to treat for a moderate treatment effect for neuropathic pain is 4-10, we set the NNT at 5 and the absolute risk reduction (ARR) between the control and the intervention groups as 0.2. Given the ARR value of 0.2, we hypothesized that after three sessions of the active taVNS, the incidence of moderate to severe uterine contraction pain on the third postoperative day would be reduced to 15%. The sample size calculation for comparing two proportions was performed using the Z-Test with Unpooled Variance. The power calculation employed the Normal Approximation method, with a Two-Sided Alternative Hypothesis specified to assess statistical significance of the proportional difference. The

test type was defined as Unpooled Z-Test to accommodate potential between-group variance heterogeneity. A strategy of equal sample allocation ( $N_1 = N_2$ ) was adopted, with input parameters specified as proportions. With a statistical power of 0.80 and  $\alpha = 0.05$ , we calculated that a sample size of 70 patients per group was required using PASS version 15.0 (NCSS). Assuming a 10% loss to follow-up, we planned to recruit 78 participants per group.

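### The day-3 primary outcome is sized for one ungated 0.05 test, but section 3.6 routes incidence through an interaction gate and does not exempt day 3

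*Protocol*

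**What the plan says.** Protocol section 3.5.1: "The primary outcome is the incidence of moderate to severe uterine contraction pain on the third postoperative day". An event is defined by a cut-off: "uterine contraction pain is classified as moderate to severe if the VAS score is 4 or higher".

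Protocol section 3.7 compares two proportions on that day, 35% under sham and 15% under active stimulation. The calculation was "performed using the Z-Test with Unpooled Variance", two-sided, with alpha 0.05 and power 0.80: "we calculated that a sample size of 70 patients per group was required using PASS version 15.0". Allowing for 10% loss gives 78 per group. There is no gate and no division of alpha.

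Protocol section 3.6 sets one rule for outcomes measured repeatedly. A GEE is fitted and the treatment-by-time interaction is tested first. If it is significant, "we will test the between-group differences at each time point and use the Bonferroni test to adjust for multiple comparisons". If it is not, the treatment main effect is tested and "the Bonferroni correction will not be performed for the treatment effects at each time point". The section then lists the incidence of moderate to severe contraction pain among the outcomes modelled this way, with a logit link and terms for group, time and their interaction. It does not say which visits enter that model, and it does not single out day 3. Chi-squared and Fisher tests appear in the opening paragraph, for categorical variables in general, introduced as descriptive statistics.

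Protocol section 3.5.2 measures contraction pain at T1 to T7, where T7 is day 3. Every secondary outcome listed there is a score or scale; none is an incidence.

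**The concern.** Three sections describe the primary comparison, and they do not fit together. Sections 3.5.1 and 3.7 describe one binary comparison at one time, tested once at 0.05. Section 3.6 describes a path chosen by the data. On one branch day 3 is one of several contrasts at a reduced alpha. On the other, the test named is an average over visits, which is a different question from the one in section 3.5.1. Since no secondary outcome is an incidence, the incidence GEE most likely serves the primary outcome.

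What is at stake is which result makes the trial positive. A single pre-specified primary comparison needs neither a gate nor a multiplicity correction. If the path in section 3.6 is followed, a true day-3 effect of the planned size may be missed more often than planned. A significant main effect could also come largely from earlier visits, and would not by itself show a day-3 benefit.

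**Working it through.** **Inputs.** From section 3.7: p1 = 0.35, p2 = 0.15, two-sided alpha 0.05, power 0.80, 70 per group, unpooled Z-test. From section 3.5.2: contraction pain at seven times, T1 to T7. Assumed: K, the number of visits in the incidence GEE. K = 7 is the natural reading; 2 and 3 are shown to give the range.

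**Step 1: reproduce the sample size.**
n = [p1(1−p1) + p2(1−p2)] × (z0.975 + z0.80)² / (p1−p2)²
= (0.2275 + 0.1275) × (1.960 + 0.842)² / 0.20² = 69.66, rounded up to 70. Then 70/0.90 = 77.8, so 78. The stated figures reproduce exactly.

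**Step 2: power at 70 per group for a single day-3 test.**
z = 0.20/√(0.355/70) = 2.81; power = Φ(2.81 − 1.96) = 0.802.

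**Step 3: the same comparison with alpha divided by K** (the significant-interaction branch).

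| K | alpha | Power, 70 per group | n per group for 80% | Recruited, 10% loss |
|---|---|---|---|---|
| 1 | 0.05 | 0.802 | 70 | 78 |
| 2 | 0.025 | 0.715 | 85 | 95 |
| 3 | 0.0167 | 0.661 | 93 | 104 |
| 7 | 0.0071 | 0.547 | 111 | 124 |

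For K = 7: Φ(2.81 − 2.69) = 0.547. If all 78 were evaluable it would be 0.608. A Wald test on the logit scale, which is what the GEE would give, has lower power: about 0.49 for K = 7.

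**Step 4: simulate the whole path.** 70 per group; 4,000 runs per scenario; saturated logit GEE with independence working correlation and robust covariance; latent correlation 0.3 or 0.6. Every scenario ends at 35% against 15% on day 3. The protocol gives no incidence at other visits, so these are assumptions. With 7 visits, sham rates are either 35% throughout or fall 70, 65, 60, 55, 50, 45, 35%. With 3 visits they are 60, 50, 35%. Effects before day 3 are fractions of the day-3 log odds ratio.

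Reading A: success is a significant interaction plus day 3 significant at 0.05/K, or a non-significant interaction plus a significant main effect. Reading B: the second branch allows an uncorrected day-3 test instead.

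| Visits | Effect pattern | Reading A | Reading B | Direct day-3 test |
|---|---|---|---|---|
| 7 | T7 only | 0.43–0.45 | 0.62–0.67 | 0.78–0.79 |
| 7 | T6 and T7 | 0.50–0.51 | 0.53–0.55 | 0.77–0.79 |
| 7 | growing gradually | 0.58–0.70 | 0.61–0.66 | 0.78–0.79 |
| 7 | half size T2 to T6 | 0.60–0.79 | 0.67–0.73 | 0.78–0.79 |
| 7 | constant from T2 | 0.62–0.70 | 0.57–0.62 | 0.77–0.80 |
| 3 | day 3 only | 0.63–0.64 | 0.69–0.73 | 0.79–0.80 |
| 3 | growing gradually | 0.78–0.86 | 0.76–0.77 | 0.78–0.79 |
| 3 | constant | 0.95–0.97 | 0.78–0.79 | 0.78–0.80 |

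**Step 5: what the main effect measures.** Taken alone with 7 visits, the main effect is significant in 0.10–0.13 of runs when the effect is on day 3 only, and in 0.94–1.00 when it is constant from T2. It tracks the average over visits, which with T1 to T7 includes a visit before any stimulation. The values above 0.80 in the three-visit rows under reading A arise through this average.

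**The case against.** The strongest reply is that chi-squared or Fisher is the intended primary test. Section 3.6 opens with it for categorical variables, limits the gated rule to data collected at several times, and does not mention day 3 in the incidence GEE sentence. The label of descriptive statistics is not decisive, because the same paragraph also sets out between-group t-tests and Mann-Whitney tests. A chi-squared test would also fit the sample size closely. This stands as a possible reading. It does not remove the problem: the test is not assigned to the primary outcome, and the only analysis named for this incidence is the gated GEE. A separate analysis plan might settle the matter, but the protocol would still contain the conflicting rule.

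A second reply also stands: T1 to T7 is inferred from the pain-score schedule. The number of visits in the incidence model is not stated, and fewer visits soften the loss. The simulated ranges rest on assumed time courses.

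Some stronger inferences are not supported. A reader might conclude that the gate inflates the day-3 type I error, but neither branch tests day 3 at a threshold above 0.05. A reader might also treat a main effect driven by earlier visits as a false positive for the primary outcome. It is one only if reported as the day-3 result, which section 3.6 does not say. Nor is the sample-size arithmetic wrong.

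**Conclusion.** The inconsistency stands. The 80% power in section 3.7 belongs to one ungated day-3 comparison at two-sided 0.05. Section 3.6 does not commit to that comparison, and its only incidence-specific rule does not match it. At best the protocol leaves two conflicting primary tests.

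The firmest figures are by formula: if Bonferroni applies to day 3, power falls from 0.80 to 0.72, 0.66 or 0.55 for 2, 3 or 7 visits. Over the whole path with 7 visits, success was about 0.43–0.79, against 0.77–0.80 for the direct test. If the second branch permits an uncorrected day-3 test, it was about 0.53–0.73 with 7 visits and 0.69–0.79 with 3.

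A reader might infer that the trial is certain to fall short of 80% under section 3.6. That goes too far: with 3 visits and an effect present throughout, overall success can exceed 0.80. It does so through an effect averaged over visits, which does not answer the day-3 question.

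**What to change.** State in section 3.6 that the sole primary test is the active-versus-sham contrast in the proportion with moderate to severe contraction pain at T7, at two-sided alpha 0.05, not conditional on the interaction test and not Bonferroni-corrected. Name the method: a two-proportion test or the T7 contrast from the GEE would serve. Preferably report it as a risk difference with 95% confidence interval, since the sample size is built on an absolute risk reduction. The choice of effect measure is a recommendation; resolving the conflict needs only the named test.

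Keep the repeated-measures GEE (interaction, main effect and other visits) as secondary, and state which visits the incidence model includes.

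The cost is a wording change before unblinding; the planned 70 evaluable (78 recruited) per group remains adequate under its own assumptions. If the gated procedure is to be kept for the primary outcome, the sample size has to be redone for it. For the Bonferroni-corrected day-3 contrast alone, 80% power would need 93 per group (104 recruited) with 3 visits or 111 (124 recruited) with 7.

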### **3.4 Follow-up Plan**

On the day before the parturient's surgery (T0), researchers will collect baseline data, and assess sleep at T0 on the morning of the surgery. On the day of the surgery, before the first intervention (T1), blinded researchers will evaluate the peak uterine contraction pain and incision pain. After the first intervention (T2), depression and anxiety will be assessed, followed by re-evaluation of peak uterine contraction pain and incision pain during this period. Sleep at T2 will be assessed on the morning of the first postoperative day. Before the second intervention (T3), peak uterine contraction pain and incision pain will be evaluated. After the second intervention (T4), depression, anxiety, postpartum recovery quality, and peak uterine contraction pain and incision pain during this period will be assessed. Sleep at T4 will be evaluated on the morning of the second postoperative day. Before the third intervention

(T5), peak uterine contraction pain and incision pain will be evaluated. After the third intervention (T6), depression, anxiety, postpartum recovery quality, and peak uterine contraction pain and incision pain during this period will be assessed. On the morning of the third postoperative day (T7), sleep at T6 will be evaluated, along with peak uterine contraction pain, incision pain, depression, anxiety, and postpartum recovery quality. At 1 month postpartum (T8), the telephone follow-up will assess the parturient's depressive and anxiety status.

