#### **3.5.2 Secondary outcomes**

1) Peak uterine contraction pain scores during the three days postoperatively (assessed by the VAS). The contraction pain scores are measured before the

first intervention (T1), after the first intervention (T2), before the second intervention (T3), after the second intervention (T4), before the third intervention (T5), after the third intervention (T6), and the third postoperative day (T7).

2) Incision pain scores at T1-T7 (assessed by the VAS).

3) Maternal anxiety scores at T2, T4, T6, T7 and the first month postpartum [T8] (assessed by the Pregnancy-Related Anxiety Questionnaire-Revised 2 [PRAQ-R2], comprising 10 items, each rated on a 5-point scale [1-5], with higher scores indicative of increased pregnancy-related anxiety).

4) Maternal depression scores at T2, T4, T6, T7, and T8 (assessed by the Edinburgh Postnatal Depression Scale [EPDS], including 10 items, scored on a 4-point scale [0-3], with higher scores denote more severe depressive symptoms).

5) Sleep quality at T2, T4 and T6 (assessed by the Leeds Sleep Evaluation Questionnaire [LSEQ], with higher scores indicating better sleep quality).

6) Quality of postpartum recovery at T4, T6 and T7 (assessed by the 11-item Obstetric Quality Recovery Scale [ObsQoR-11], with a total score range of 0-110).

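### For depression and anxiety, whether the one-month rating gets its own answer depends on an interaction test the trial was not sized for; otherwise it is pooled with four ward ratings into one main effect

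*Protocol*

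**What the plan says.** Protocol section 3.5.2 lists "Maternal depression scores at T2, T4, T6, T7, and T8", and the same five times for anxiety. Section 3.4 places the first four between the day of surgery and the morning of the third postoperative day. The fifth is different: "At 1 month postpartum (T8), the telephone follow-up will assess the parturient's depressive and anxiety status". Under section 3.8 the three stimulation sessions fall on the day of delivery and the two days after it. T8 is therefore the only efficacy rating taken well after treatment has ended.

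Section 3.6 gives each repeated score one GEE with group, time and group by time, with these settings: "link function: identity link; group variable: participant; intraclass correlation structure: independent". A two-step rule governs the conclusion. The first branch reads: "If this interaction is significant, we will test the between-group differences at each time point and use the Bonferroni test to adjust for multiple comparisons". The second reads: "Otherwise, we will next test the main effect of treatment, and the Bonferroni correction will not be performed for the treatment effects at each time". The threshold is P < .05 throughout. The protocol states no separate one-month contrast and no weighting of visits. It also does not say whether time enters as a factor or as a continuous covariate.

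**The concern.** The effect during and just after treatment and the effect a month later are two separate questions. The rule answers the second one directly only when the interaction test is significant. When it is not, the conclusion is a pooled effect whose weights reflect how often women were rated on the ward, not a stated question.

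Two misreadings follow. A benefit confined to the hospital stay can be concluded as one effect over follow-up to one month, although there is none at T8. A benefit that appears only at T8 can go undeclared because the interaction test did not open the per-visit branch.

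**Working it through.** **The protocol's own figure.** Section 3.7 sizes the trial on 35% versus 15%, two-sided alpha 0.05, power 0.80, unpooled Z-test:

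n = [0.35×0.65 + 0.15×0.85] × (1.960 + 0.842)² / 0.20² = 69.66, so 70 per group; 70/0.9 gives 78 recruited.

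This reproduces. It concerns the day-3 pain incidence only. No figure is given for depression, anxiety or an interaction.

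**Weights.** With time as a factor and complete data, the main effect under an independent working correlation is the plain mean of five visit differences: 4/5 = 80% ward, 1/5 = 20% month 1. If the main effect is refitted without the interaction and T8 has losses, the ward share rises: 4×78/(4×78+70) = 81.7%, and 4×78/(4×78+62) = 83.4%.

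**Assumptions for power (none given in the protocol).** 70 per group, SD 1, correlation r among ward ratings and r8 between ward and T8. Three sets of (r, r8) were used: (0.7, 0.3), (0.5, 0.5) and (0.8, 0.5).

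**T8 on its own.** SE = √(2/70) = 0.169. For 0.5 SD, 0.5/0.169 = 2.96, and power is Φ(2.96 − 1.96) = 84%. At the Bonferroni level 0.05/5 = 0.01 it is Φ(2.96 − 2.58) = 65%, before allowing for the need to pass the interaction test first.

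**Interaction test (4 df).** For an effect d on all ward visits only, or at T8 only, the non-centrality is d²/V, where V = (2/70) × [(1+3r)/4 + 1 − 2·r8]. For (0.7, 0.3), V = 0.02857 × 1.175 = 0.0336. With d = 0.4 the non-centrality is 0.16/0.0336 = 4.8, giving power 38%.

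**Main effect.** For (0.7, 0.3), the variance is (2/70) × (5 + 12×0.7 + 8×0.3)/25 = 0.0181, so SE = 0.134. A ward-only effect of 0.4 SD gives a mean of 0.32 SD and power of 66%. A T8-only effect of 0.5 SD gives a mean of 0.10 SD and power of 11.5%.

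**Full two-step rule**, simulated with 200,000 draws of the five visit differences:

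| Quantity | (0.7, 0.3) | (0.5, 0.5) | (0.8, 0.5) |
|---|---|---|---|
| *0.4 SD at T2–T7, none at T8* | | | |
| Interaction significant | 38% | 66% | 51% |
| Interaction not significant and main effect significant | 38% | 23% | 26% |
| *0.5 SD at T8 only* | | | |
| Interaction significant | 57% | 87% | 73% |
| T8 declared, Bonferroni branch only | 46% | 62% | 54% |
| T8 declared, unadjusted tests also allowed after a non-significant interaction | 77% | 69% | 72% |
| Prespecified T8 contrast at 0.05 | 84% | 84% | 84% |
| *0.5 SD at all five ratings* | | | |
| Main effect significant | 96% | 97% | 93% |

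For a T8-only effect of 0.3 SD, T8 is declared in 10–15% of trials through the Bonferroni branch and in 32–37% if unadjusted tests are also allowed, against 43% for the prespecified contrast.

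**The case against.** Several points on the other side stand.

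- T8 is not always averaged away. After a significant interaction it is tested alone, at about 0.01.
- The sentence on the second branch can be read as leaving per-visit effects to be reported without adjustment. On that reading the shortfall at T8 is smaller (69–77% against 84%), and a null result at T8 would at least be visible.
- A reader might infer that a lasting benefit would mostly be missed. The documents do not support that. A lasting benefit is present on the ward and at T8, and for 0.5 SD throughout, the main effect detects it in 93–97% of trials, more often than T8 alone (84%). The loss concerns a delayed effect only.
- A reader might also infer that the move to the telephone biases the one-month comparison. It applies to both arms of a randomized, blinded trial, so it does not by itself confound the between-group difference, and section 3.6 plans no interpretation of the change from T7 to T8.
- The 80% share assumes time as a factor, which the protocol does not state.
- These are two of six secondary outcomes. The primary outcome and sample size are untouched, and the choice of contrasts to display is often left to an analysis plan.

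The last point does not dispose of the matter. The protocol does not leave the decision open: it states a rule, and that rule makes the one-month conclusion conditional on the interaction test.

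**Conclusion.** The concern holds in a limited form. For EPDS and PRAQ-R2 the only post-discharge efficacy result depends on an interaction test for which the trial was not sized, and the fallback is a main effect weighted 80:20 towards the ward days if time is a factor and data are complete.

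The clearest harm is over-generalisation: with a ward-only effect of 0.4 SD, about 23–38% of trials would report a single overall effect. The second harm is lost power for a delayed T8-only effect of 0.5 SD: 46–62%, or 69–77% on the more lenient reading, against 84%. All these figures rest on assumed effect sizes and correlations with 70 per group. A sustained effect is not at risk. The point deserves a change to the text but does not touch the primary result.

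**What to change.** In section 3.6, for EPDS and PRAQ-R2, state that time enters the GEE as a factor and prespecify two contrasts from that same model: the mean between-group difference over T2, T4, T6 and T7, and the between-group difference at T8. Report each with a 95% CI whatever the interaction test shows.

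The cost is a sentence or two, with no new data and no second model. The small downside is two secondary estimates per scale instead of one.

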### **3.3 Randomization and Blinding**

Participants are randomly assigned in a 1:1 ratio to either the active taVNS group or the sham taVNS group based on a computer-generated random number sequence. The allocation information is concealed in opaque envelopes and remains concealed until participants are ready to initiate the first intervention in the ward. All personnel involved in data collection, processing, and analysis, as well as other healthcare staff and participants, are blinded to the group assignments. Blinding will be disclosed after statistical analysis of the trial results.

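### Section 3.6 leaves per-time treatment effects uncorrected after a non-significant interaction, and does not place the single-time primary outcome outside the rule

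*Protocol*

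**What the plan says.** Protocol section 3.6 sets one rule for all data measured at several times: "First, we will test the interaction between treatment and time". If that test is significant, the groups are compared at each time with Bonferroni. If it is not, the main effect of treatment is tested and "the Bonferroni correction will not be performed for the treatment effects at each time point". The only threshold given is P < .05 "considered statistically significant". The rule is followed by the GEE settings, with group, time and their interaction as covariates, for the incidence of moderate to severe contraction pain and for six scores.

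Section 3.5.2 gives the times for the scores:
- contraction pain and incision pain: T1 to T7 (seven)
- anxiety and depression: T2, T4, T6, T7, T8 (five)
- sleep: T2, T4, T6 (three)
- recovery quality: T4, T6, T7 (three)

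T1 is before the first intervention (section 3.4). The primary outcome in section 3.5.1 is the incidence on the third postoperative day, a single time. Section 3.7 sizes the trial for that one comparison, "with a Two-Sided Alternative Hypothesis specified to assess statistical significance of the proportional difference", at alpha 0.05.

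**The concern.** A non-significant interaction gives no support for picking out single times, so the main effect is the natural summary. The last clause of that branch nevertheless speaks of treatment effects at each time and says they will not be corrected. If those effects are tested at 0.05, protection is absent where it is most needed: with no treatment effect, nearly every trial enters this branch. An isolated day could then be called significant for pain, mood, sleep or recovery well above 5% of the time, although the plan mentions Bonferroni.

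The second problem concerns the primary outcome. The rule covers everything measured repeatedly, and the incidence of moderate to severe pain is given a group-by-time model directly below it. Nothing exempts the third-day contrast. Depending on the interaction test, the primary comparison could be a Bonferroni-adjusted contrast or a main effect over all modelled times. Neither is the test that the trial was sized for.

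**Working it through.** **1. The plan's own figure.** Inputs from section 3.7: 35% versus 15%, two-sided alpha 0.05, power 0.80, unpooled Z-test, equal groups.

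n = (z₀.₉₇₅ + z₀.₈₀)² × [p₁(1−p₁) + p₂(1−p₂)] / (p₁−p₂)² = (1.960 + 0.842)² × (0.2275 + 0.1275) / 0.04 = 69.66, so 70 per group. The plan's figure is reproduced. It belongs to one unadjusted test at one time.

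**2. Primary outcome under the first branch.** With 70 per group, SE = √(0.355/70) = 0.0712 and 0.20/0.0712 = 2.808.
- At alpha 0.05: Φ(2.808 − 1.960) = 0.80.
- At alpha 0.05/7 = 0.00714, critical value 2.690: Φ(2.808 − 2.690) = 0.55.

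Seven times in the incidence model is an assumption; the protocol does not give the number.

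**3. Upper bound for uncorrected per-time tests.** With m independent tests at 0.05 and no interaction gate, 1 − 0.95^m is 14.3% (m = 3), 22.6% (m = 5) and 30.2% (m = 7).

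**4. The full two-branch rule under no effect.** This was simulated with 400,000 draws of normal z-statistics for the between-group difference at m times. The interaction was a Wald test on m−1 df at 0.05. If significant, each time was tested at 0.05/m; if not, each time was tested at 0.05. The protocol gives no within-woman correlation, so an exchangeable value from 0 to 0.9 was assumed. The interaction was non-significant in about 95% of draws.

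Chance of at least one false-positive time per outcome:

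| Correlation | 3 times | 5 times | 7 times (T1–T7) | T2–T7 only |
|---|---|---|---|---|
| 0 | 12.3% | 20.2% | 27.5% | 24.0% |
| 0.3 | 12.1% | 18.5% | 24.4% | 21.5% |
| 0.5 | 11.3% | 16.4% | 20.7% | 18.6% |
| 0.7 | 10.0% | 13.5% | 16.3% | 15.0% |
| 0.9 | 7.8% | 9.4% | 10.6% | 10.1% |

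The last column keeps the seven-time rule but does not count a T1 difference, which cannot be a treatment effect. A separate simulation with 70 women per arm, an estimated covariance and 8,000 replicates gave 25.3%, 20.9% and 15.5% for seven times at correlations 0.3, 0.5 and 0.7, in close agreement.

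**5. The other readings, same simulation.**
- Second branch is the main-effect test only: about 5–7% chance of any false positive per outcome, for 3, 5 or 7 times.
- Per-time tests only after a significant main effect: 4.9–5.9%.
- Bonferroni in both branches: 2.0–4.9%.

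**The case against.** The strongest reply is that the protocol orders per-time testing only after a significant interaction. The other branch names one test, the main effect. The final clause can be taken to mean only that the per-time Bonferroni step does not apply there, which gives about 5–7%. The text never expressly says that per-time tests will be run or interpreted in that branch. This stands as a limit on the claim. It does not remove the point: if only the main effect is tested there is nothing to correct, so the clause has a function only if per-time effects are assessed. The literal reading is the more natural one.

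A reader might infer three stronger things that the protocol does not support:
- *That the rule is back to front.* It is not. Interaction first, adjusted per-time tests if significant and a main effect otherwise is a usual sequence; only the last clause is at fault.
- *That false-positive times are frequent for every repeated outcome.* With three times (sleep, recovery) the figure is only about 8–12%, it falls as correlation rises, and T1 should not count for the pain scores.
- *That the incidence model is known to use seven times.* The protocol does not say so.

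It is also fair that the six scores are secondary and that no familywise control is claimed for them. Presentation detail could be left to an analysis plan, but here the protocol itself fixes the rule, and its wording reaches the primary outcome.

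**Conclusion.** The point holds for the final clause and for the missing exemption of the primary outcome, not for the sequence as a whole. On the literal reading, the chance of at least one false-positive time per outcome is about 8–12% (sleep, recovery), 9–20% (anxiety, depression) and 10–24% for the pain scores over T2–T7 (11–28% with T1 counted). On the main-effect-only reading it is about 5–7%. These figures assume no treatment effect at any time, exchangeable correlation between 0.9 and 0, and normal test statistics with known variance; robust GEE standard errors at about 70 per arm would shift them slightly.

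For the primary outcome, power would be about 55% instead of 80% if seven times share a Bonferroni correction. In the other branch, the named test would be a main effect that may include the pre-intervention T1. Both consequences depend on how many times enter the incidence model. A rule whose error rate runs from about 5% to 28% according to how one clause is read, and which leaves the primary test dependent on a preliminary test, should be rewritten before analysis.

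**What to change.** Change section 3.6 in two places.

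1. State that the primary test is the single between-group contrast in the incidence of moderate to severe contraction pain on the third postoperative day (T7), at two-sided 0.05, outside the interaction and Bonferroni rule. This matches section 3.7.
2. For the secondary repeated outcomes, replace the last clause. With a non-significant interaction, inference rests only on the main effect over post-intervention times, and per-time estimates are shown with 95% confidence intervals as description, without p-values. With a significant interaction, Bonferroni is applied over the post-intervention times, leaving out T1.

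The cost is a few sentences and fewer per-day p-values to report. The sample size does not change.
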